# 1 Rationale and background information

Worldwide, health care systems are facing immense challenges: As life expectancy increases at unprecedented levels, an ever-growing aging population suffers from non-communicable, chronic disease (WHO, 2013). In order to address these problems with the limited financial and human resources available, new ways of delivering healthcare need to be explored. Tele-solutions (e.g. telehealth, telemonitoring, eHealth and mHealth services) are increasingly employed to enable the delivery of accessible, high-quality and cost-effective remote healthcare (WHO, 2011).

COPD and CHF are two long-term conditions, known for high re-hospitalisation rates and their severe impact on life expectancy and activities of daily living due to frequent symptoms of fatigue and dyspnoea that limit several aspects of their life, making patients dependent on others in their daily living (GOLD, 2013). Patients with CHF and COPD are mostly elderly and require hospital care frequently. Although pharmacological therapy has improved outcome markedly over the last 10-15 years, management programs are needed to optimize care (Holland et al., 2005). Being affected by a chronic disease with a high symptom burden is a challenge to living a fulfilled life. Support and training to enable successful self-management positively impacts on health behaviour, health status and health care utilization.

The World Health Organization and Institute of Medicine at the US National Academy of Sciences have identified person-centred care (PCC) as a core concept for the delivery of care in the chronically ill patient (Epping-Jordan, Pruitt, Bengoa, & Wagner, 2004; Organization., 2008). In PCC, the relationship between health care professional and patient is characterized by equality: professional and patient jointly develop a personal health plan using resources identified in each patient's illness history but also by defining potential barriers (Ekman et al., 2011). GPCC research demonstrated the beneficial effect of PCC (shortened hospital stays) in a hospital environment (Ekman et al., 2012) as well as in relieving uncertainty of the condition and its treatment (Dudas et al., 2013).

C4 aims to deliver person-centered care (PCC) utilizing information and communication technology (ICT) for people with chronic heart failure (CHF) and / or chronic obstructive pulmonary disease (COPD).

Within this research project we will develop and test a telephone support service and ICT platform to provide information, training and professional support for patients. Patients will keep and manage their own health record ('Health Plan').

The goal is to enable patients to understand their disease and therapy better, to identify their own resources to enhance coping and living with their chronic illness by means of a dialogue and partnership between health carer and patient. This will be an advice-only service that does **not entail** changes in medical treatment plans or advice regarding medical decisions, investigations.

## *Aims of the project*

The goal of the two phases (Phase I and Phase II) of the research project C4' described in this plan is to translate the PCC principles into a tele context.

## *Project design*

This project is a complex intervention and as such features a multitude of influencing factors (May, Mair, Dowrick, & Finch, 2007) The study design was guided by the new Medical Research Council's (MRC) framework for complex interventions (Craig et al.,

2008). We opted for the revised version of the original MRC framework due to its iterative approach and increased focus on early phase piloting and development of complex intervention.

The two phases of the C4 project correspond with the three steps of *Development and Feasibility and Piloting* and *Evaluation* of the MRC framework (Craig, et al., 2008). The *implementation* of the intervention into a large context will be planned according to the results of this preliminary study in a follow-on protocol.

As the blue arrows in Figure 1 above indicate, *Development, Feasibility and Piloting*, and *Evaluation* are not distinct, stand alone phases in the MRC framework, but stages that may be revisited iteratively to allow for maximum flexibility and optimisation of the intervention and its delivery. The two phases of our project reflect this flexible and iterative approach as we embedded an RCT study into a number of qualitative subprojects. During phase I (April 2014 until October 2014), the preparation phase, we will develop the intervention and test the procedures. The development will be guided by qualitative interview studies aimed at exploring patients support needs and the nurse-patient relationship in telecare. The knowledge gained in this phase will inform the development of the actual intervention.

During phase II (October 2014 until December 2015), we will test and evaluate the procedures with in an RCT supplemented by qualitative studies. The quantitative study, an RCT will be conducted to research projects to evaluate our primary endpoints (patient and carer outcomes and economic evaluation of the intervention). While the quantitative assessment is essential to demonstrate the effect of the intervention on health care utilization and patient outcomes, we decided to supplement this study with various qualitative subprojects. This will enable us to obtain feedback on the impact of the intervention on patients and their informal carers, but also the effect on nurses who deliver a PCC based intervention.

The two phases and their subprojects will be described in detail in the respective sections of this study plan.

Figure 1 gives an overview of the two main phases of the project.

[figure not shown]

Figure 1: Phases I and II of C4 within the MRC framework (Craig, et al., 2008)

## 2 Project Plan phase I – Preparation (April 2014 – October 2014)

During phase I, we will explore patient needs and nurses perspectives on the delivery of remote health-care through qualitative interview studies. The results obtained in both studies will inform the design and delivery of the patient intervention.

### 2.1 Interview study exploring patients' support needs

|                              |                                                                                                                                                                                                                                                                                                                                                                                                      |
|------------------------------|------------------------------------------------------------------------------------------------------------------------------------------------------------------------------------------------------------------------------------------------------------------------------------------------------------------------------------------------------------------------------------------------------|
| Background                   | Patients suffering from chronic obstructive pulmonary disease (COPD) and/or chronic heart failure (CHF) experience a host of restrictions in daily life. Apart from physical restriction, they have to cope with anxiety, fear of living as well as fear of dying, fear of the future and a reluctance to engage with the feelings triggered by the disease (Strang, Ekberg-Jansson, & Henoch, 2013) |
| Aim                          | To investigate the need for PCC in patients suffering from COPD and/or CHF.                                                                                                                                                                                                                                                                                                                          |
| Research Question            | What are the care needs of patients suffering from COPD and/or CHF?                                                                                                                                                                                                                                                                                                                                  |
| Method                       | Individual interviews, semi structured.                                                                                                                                                                                                                                                                                                                                                              |
| Sample & sampling            | A convenience sample of 15-20 (depending on point of data saturation) volunteers affected by COPD and/or CHF, recruited via a facebook page for peer-support (Lugna Lungor), patient organizations ('Riksförbundet HjärtLung') and a flyer (Verdandi) between April-August 2014.                                                                                                                     |
| Data collection and analysis | Individual interviews with patients suffering from COPD and/or CHF, to be transcribed and content analysed (Graneheim & Lundman, 2004; Krippendorff, 2004).                                                                                                                                                                                                                                          |
| Ethical considerations       | The respective ethics committee was contacted and presented with the study proposal. The committee raised no concerns and did not require a full application for ethical approval. Written informed consent (Appendix A) was obtained from all participants. Personal identifiable data will be coded in the transcription.                                                                          |
| Investigators                | [name], [name], [name]                                                                                                                                                                                                                                                                                                                                                             |

## 2.2 Interview study focussing on the experience of nurses working in telecare

|                   |                                                                                                                                                                                                                                                                                                                                                                                                                                          |
|-------------------|------------------------------------------------------------------------------------------------------------------------------------------------------------------------------------------------------------------------------------------------------------------------------------------------------------------------------------------------------------------------------------------------------------------------------------------|
| Background        | Registered nurses (RNs) who deliver care from call-centres have no face-to-face encounters with patients. While some studies have explored the role of the RNs working in tele-care to some extent (Chang, Lee, & Mills, 2013; Doolittle, 2001), in-depth studies exploring the tele care relationship between patient and nurse, as well as the challenges and opportunities which are associated with tele- care delivery are lacking. |
| Aim               | To explore the possibility of integrating PCC concepts into a telehealth context.                                                                                                                                                                                                                                                                                                                                                        |
| Research Question | How do nurses perceive their call center environment to differ from a traditional hospital ward or clinic environment?                                                                                                                                                                                                                                                                                                                   |

|                              |                                                                                                                                                                                                                                                                                                                                                                                                                                                           |
|------------------------------|-----------------------------------------------------------------------------------------------------------------------------------------------------------------------------------------------------------------------------------------------------------------------------------------------------------------------------------------------------------------------------------------------------------------------------------------------------------|
|                              | 
How does the remote care delivery and their virtual presence alter the patient – nurse relationship?
 
How does the remote care delivery affect RN's professional identity and role?
 
Where are the barriers and opportunities to the delivery of person-centred care in a telecare context?
                                                                                                                                            |
| Method                       | Focus group interviews, semi-structured.                                                                                                                                                                                                                                                                                                                                                                                                                  |
| Sample & sampling            | 4 focus groups with a total of 21 RNs working in a German telehealth centre.                                                                                                                                                                                                                                                                                                                                                                              |
| Data collection and analysis | 
Data analysis: Qualitative content analysis (Graneheim & Lundman, 2004; Krippendorff, 2004)
 
Semi-structured focus groups interview study with RN's working in a telehealth centre in Southern Germany. The centre provides care for more than 10000 chronically ill patients across the country.
                                                                                                                                        |
| Ethical considerations       | 
The protocol for this study was reviewed by the respective German ethical committee: Ärztekammer Bayern Ethikkommission, Bayerische Landesärztekammer in Munich in May 2014 and declared as ethically safe. The committee raised no concerns and did not require a full application for ethical approval. Written informed consent (Appendix B) was obtained from all participants. Personal identifiable data will be coded in the transcription.
 |
| Investigators                | [name], [name], [name], [name]                                                                                                                                                                                                                                                                                                                                                                                                       |

### 2.3 Preparation of nurses for delivery of tele-support

To prepare nurses to deliver PCC care through a training program based on the principles for Person-centred Care as outlined by Ekman et al. (2011).

**Proposed contents of nurse training (as identified during workshop on 18/19 August 2014)** Nurses will develop and practice their skills under the guidance of experienced mentors ([name] and [name])

**The training will include the following aspects, it will be developed based on the feedback from the nurses.**

Medical knowledge about COPD and CHF

Areas that will need to be addressed in the theoretical training on facts about COPD and CHF as identified in the workshop are:

- COPD and CHF as a disease, symptoms, causes, disease progression, treatment, etc.
- Medicines, their use, side effects, administration
- Medical technical products (e.g. inhalers) and their use
- Frequent patient questions about disease and its management
- Knowledge about co-morbidities that affect the patients, such as diabetes

Living with COPD/ CHF

Knowledge about resources for the patient and how to access these.

- Formal support structures that exist within the community (mobile team, COPD teaching group, access to specialist nurses and doctors etc.)

- Informal support structures: patient groups, networks for patients and informal carers
- Advice on daily living: Organize training sessions for nurses with
  - 'Occupational therapist'
  - 'Physiotherapist'
  - 'Dietician'

#### Eliciting the patient narrative: Communication techniques

The patient narrative is the key to establishing a person centred partnership between patient and nurse, to identify the patient's goals and resources, and to document these in a mutually agreed Health plan.

The communication training will need to comprise practical and theoretical elements.

Theoretical elements:

- Motivational interviewing
- Person-centred Communication as per gPCC (Fors, 2014)
- Enabling and sense making model of communication (Ohlen, Wallengren Gustafsson, & Friberg, 2013)

Practical elements:

- Simulation of telephone conversations with patient representatives and nurses
- Recording of communication, reflection and analysis on person-centredness of conversation with mentors and peers

#### Coaching and Counselling skills

In order to enable patients

- To become more equal in their encounters with other health professionals such as their cardiologist, pulmonologist or General Practitioner, patients need to feel confident and possess relevant knowledge. Coaching and counselling to take a more active in decision-making processes in clinical will be part of the tele-support service.
- To better learn to manage the anxiety and fear associated with having to live with the symptoms of a chronic disease (e.g. guiding patients towards resources such as mindfulness training)

Theoretical elements: Introduction into coaching and counselling

Practical elements:

- Simulation of telephone conversations with patient representatives and nurses
- Recording of communication, reflection and analysis on person-centredness of conversation with mentors and fellow nurses

#### Building an equal partnership

Theoretical elements: Exploring the philosophical underpinnings of PCC.

Practical elements: Personal reflection in learner's diary, informal reflection within research group

#### Documentation and personal Health plan

Theoretical elements: Input sessions on documentation and personal Health plan as per gPCC principles.

Practical elements: Reflection and practical utilization in peer discussion and teaching sessions.

### 3 Project plan phase II- Evaluation- (October 2014 – December 2015)

#### *A Person- centred Care-based tele-support for patients (PCC-PTS)*

This intervention, based on the definition of PCC as per Ekman et al (2011), will rest on four 'pillars': *Personal health plan, Educational package, Coaching & counselling, Symptoms & signs.*

Below is a description of the overall project, followed by brief descriptions of the individual subprojects.

#### 3.1 Aim

Within the C4 program, we aim to deliver support to patients with chronic obstructive pulmonary disease (COPD) and chronic heart failure (CHF) and their informal care givers to live better and cope more effectively with the disease burden associated with COPD and/ or CHF.

#### 3.2 Scope

The goal is to enable patients and their informal carers to understand COPD and/or CHF and the therapy better, to identify their own resources to enhance coping and living with their chronic illness by means of a dialogue and partnership between health carer and patient. This will be an advice-only service that does **not entail** changes in medical treatment plans or advice regarding medical decisions, investigations

#### 3.3 Hypothesis

Inclusion of the principles of PCC in a tele-partnership system for patients with CHF and COPD will reduce the need for medical care (primary care and hospital re-admission) amongst these patients by improving self-management, self-efficacy and collaboration in the process of care.

#### 3.4 Endpoints

##### 3.4.1 Primary endpoints

The study will be conducted under the assumption the PCC relationships can easily be created at distance. The objective is to elaborate if PCC delivered through a tele-support service aimed at patients suffering from CHF and COPD will change the primary outcome measure: self-efficacy.

#### **Primary outcome measure: Self-efficacy**

- |            |                                                                                           |
|------------|-------------------------------------------------------------------------------------------|
| Improved:  | Increase in Self-efficacy > 5 units at 6 months and has not been re-admitted to hospital  |
| Worsened:  | Death or re-admitted to hospital within 6 months or a decrease in self-efficacy > 5 units |
| Unchanged: | Self-efficacy has neither improved or deteriorated                                        |

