### **3.4.2 Secondary endpoints**

- a. Number of readmissions
- b. Change in Self-Efficacy
- c. Health care utilization, measured as the number of re-admissions, and unscheduled outpatient visits due to unplanned visits to hospital and/or vårdcentral due to symptoms of COPD and CHF

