### 3.6.5 Number of patients – Power analysis

To achieve 80 % power with an alpha-error of 0.05 for an increase in the number of patients with improved self-efficacy  $> 5$  units from 20% to 40%, the number of participants in each group (comparison and intervention) needs to comprise 91 patients. We aim to include 110 patients in each group to have some margin for withdrawals/ dropouts

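### The primary outcome and objective are called self-efficacy, but the classification rule is a composite with hospital readmission and death, so a primary result would not by itself support a conclusion on self-efficacy

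*Protocol*

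**What the plan says.** Section 3.4.1 of the protocol gives the objective as whether the tele-support service "will change the primary outcome measure: self-efficacy". The definition that follows is headed with the same name and has three categories:

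- A patient is Improved only if the score has risen by more than 5 units by month 6 and there has been no readmission.
- A patient is Worsened if any one of these applies: "Death or re-admitted to hospital within 6 months or a decrease in self-efficacy > 5 units".
- The category Unchanged is worded on the score alone, with no mention of readmission or death: "Self-efficacy has neither improved or deteriorated".

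Section 3.4.2 lists as secondary endpoints (a) "Number of readmissions", (b) "Change in Self-Efficacy" and (c) health care utilization. Section 3.3 hypothesises that the programme lowers the need for primary care and hospital readmission, with self-efficacy as one of the routes. Section 3.6.5 sizes the trial for a rise from 20% to 40% in patients whose self-efficacy improves by more than 5 units, and mentions neither readmission nor death. The protocol nowhere calls the primary outcome a composite.

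**The concern.** The objective, the outcome's name, the wording of Unchanged and the power statement all describe self-efficacy. The rule that places patients in categories measures something else. A patient who gains 10 units and is readmitted once counts as Worsened. A patient whose score does not move is Unchanged if not readmitted and Worsened if readmitted.

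This matters because the trial expects the readmission component to differ between arms. A difference in the three categories could come wholly from readmission or death, and the objective as written would turn it into a statement on self-efficacy. The reverse is also possible: a real gain in self-efficacy could be diluted by readmissions that occur equally in both arms.

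**Working it through.** **The plan's own figure.** With 20% vs 40%, two-sided alpha 0.05 and 80% power, the pooled two-proportion formula gives

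n = [1.96 × √(2 × 0.30 × 0.70) + 0.842 × √(0.20 × 0.80 + 0.40 × 0.60)]² / 0.20² = 81.2, so 82 per arm.

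The continuity correction gives (81.2 / 4) × [1 + √(1 + 4 / (81.2 × 0.20))]² = 90.9, so 91 per arm. The stated 91 is reproduced, and this point does not change it.

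**Can the primary outcome differ with no effect on self-efficacy?** The protocol gives no rates for score gain, score loss, death or readmission, so all of the following are assumptions:

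- q = 0.30, the proportion with a gain above 5 units, the same in both arms.
- w = 0.15, the proportion with a loss above 5 units, the same in both arms.
- r, the proportion who die or are readmitted within 6 months, which alone differs between arms.
- Score change is independent of r, and 91 patients per arm are analysed.

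From the definitions in 3.4.1:

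- Improved = q × (1 − r)
- Worsened = r + (1 − r) × w

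For r = 50% vs 30%, Improved is 0.30 × 0.50 = 15% vs 0.30 × 0.70 = 21%. Worsened is 0.50 + 0.50 × 0.15 = 57.5% vs 0.30 + 0.70 × 0.15 = 40.5%. The other rows follow in the same way. The last two columns give the share of simulated trials significant at the two-sided 5% level.

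| Death or readmission, control vs intervention | Improved | Worsened | Three-level rank test | Improved vs not Improved |
|---|---|---|---|---|
| 50% vs 30% | 15% vs 21% | 57.5% vs 40.5% | about 58% | about 18% |
| 40% vs 25% | 18% vs 22.5% | 49% vs 36.25% | about 36% | about 11% |
| 40% vs 30% | 18% vs 21% | 49% vs 40.5% | about 19% | about 8% |

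The rank test is the tie-corrected Wilcoxon-Mann-Whitney test on the three categories. With no difference in events it rejects in about 5%, as it should. With the continuity correction that reproduces 91, the first two figures in the last column fall to about 14% and 8%.

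**The reverse case.** Suppose the 20% vs 40% of section 3.6.5 refers to score gain alone, and readmission is the same in both arms at somewhere from 20% to 50% (assumed, and independent of score change). Improved then becomes 0.20 × 0.80 = 16% vs 0.40 × 0.80 = 32% at the low end, and 0.20 × 0.50 = 10% vs 0.40 × 0.50 = 20% at the high end. Power at 91 per arm, without continuity correction, falls from 84% to between 72% and 47%.

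**The case against.** The case on the other side has four parts, and much of it stands.

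- **The composite is defined openly and has a rationale.** All three categories stand directly under the label. Patients who die receive a category instead of a missing score, and section 3.3 treats fewer readmissions as an intended effect. A reader might infer that combining these components is itself an error. The protocol does not support that: the combination is a legitimate choice, and only its name and the objective attached to it are at fault.
- **The components are largely separable.** Secondary endpoints (a) and (b), and the readmission rates listed under Health Service utilization, would help to show where a difference came from. A null result on (b) would be a strong warning. The cover is partial, however. Death has no listing of its own, (a) counts readmissions where the rule uses any readmission, and (b) is a change where the rule uses a cut at 5 units. Nor do secondary endpoints correct what the primary objective promises to conclude.
- **The size depends on the test.** Section 3.9 leaves the primary comparison blank, which a statistical analysis plan may settle. The only comparison that the protocol quantifies is the proportion improved, where the effect is about a third of the rank-test figure. This stands, so both columns are needed.
- **The assumptions favour the concern.** They pair a 10- to 20-point difference in events with exactly zero effect on self-efficacy, although section 3.3 names self-efficacy as one of the routes to fewer readmissions. This also stands.

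A detailed table of components is reporting detail that may properly sit in a statistical analysis plan. It supports the fix but is not the core of it.

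**Conclusion.** Wrong as written: the label and objective in 3.4.1 do not match the definition beneath them. A significant primary result would show an effect on a composite of self-efficacy change, readmission and death, and a conclusion on self-efficacy alone would not follow from it.

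The mismatch rests on the text and needs no assumption. Its practical size cannot be fixed from the protocol, because it depends on assumed event and score rates, on their independence and on an unstated test. In the scenarios shown it runs from about 8% to 18% on Improved vs not Improved, and from about 19% to 58% on the three-level rank test.

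A reader might infer that the trial is likely to report a false effect on self-efficacy, or that its type I error is inflated. The documents support neither. The tests are valid for the composite, the protocol fixes no wording for the report, and the high percentages are illustrations. The number of patients is not shown to be wrong, although section 3.6.5 leaves open whether its 20% and 40% already allow for readmission.

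**What to change.** 1. In the objective and in 3.4.1, name the primary outcome a composite of change in self-efficacy, hospital readmission and death, and word the primary conclusion for that composite.
2. In 3.6.5, state whether 20% vs 40% refers to the composite Improved category or to score gain alone.
3. State that any claim on self-efficacy itself rests on secondary endpoint (b).
4. Beside the primary result, show by arm the components used for classification: gain above 5 units, loss above 5 units, any readmission, and death. This may be placed in the statistical analysis plan.

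The cost is a few sentences and one results table, with no new data because every component is already needed to classify patients. The downside is a narrower headline claim. If the 20% and 40% prove to mean score gain alone, the power statement would also have to be restated for the composite.
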